
**Fig. 2 Fig2:**
[figure not shown]
Overview of the C-Mill training

### Procedure and assessments

All outcome measurements will be collected during the assessments at the movement laboratory (Table 1). The intervention group is evaluated three times: pre C-Mill training (week 16), post C-Mill training (week 22), and at the end of the follow-up (week 38). The control group is evaluated four times: pre waiting-list (week 16), post waiting-list (week 22), post C-Mill training (week 28), and at the end of the follow-up (week 44). The assessments will follow a standardized protocol and are conducted by the primary investigator (LV) who is trained to perform the outcome measurements. As the primary investigator takes part in the training sessions, outcome assessment cannot be blinded. During all assessments, the use of orthotic devices and/or orthopedic footwear is allowed depending on the task. No other (walking) aids are allowed. If participants use any orthotic or orthopedic device during a task, this will be registered and kept constant throughout the consecutive assessments.

**Table 1 Tab1:**
[figure not shown]
Standard protocol items: Recommendations for interventional trials (SPIRIT) figure

Overview of enrollment, interventions, and assessments during the study protocol. Timepoints T_1_, T_2_, and T_3_ are applicable for participants in the intervention group and usual care group. Timepoint T_s_ is only applicable for participants in the usual care group

*NA* not applicable

### Demographic and clinical assessments

The demographic and clinical assessments are collected during the first assessment in the movement laboratory. The demographic characteristics consist of age; sex; height; weight; presence (or absence) of a genetic diagnosis and inheritance pattern; disease duration (i.e., the number of years since symptom onset); regular use of medication, orthopedic shoes or orthotic devices, or other walking aids; presence and severity of visual deficits; and number of falls in the preceding year.

Clinical assessments consist of the Spastic Paraplegia Rating Scale (SPRS) to determine disease severity [19]. Bilateral muscle strength is scored with the Medical Research Council (MRC) scale for hip adduction, abduction, flexion, and extension; knee flexion and extension; and ankle plantar and dorsiflexion [4, 20, 21]. Bilateral muscle tonus is scored with the Modified Ashworth Scale (MAS) for the hip adductors (hip 70° flexed), knee flexion and extension, and ankle plantar and dorsiflexion with knee extended (gastrocnemius) and knee flexed (soleus) [22]. Vibration sense is evaluated using a tuning fork on bilateral patella, lateral malleolus, and at the first metatarsophalangeal joint. Trunk control is assessed using the Trunk Control Measurement Scale (TCMS) [23]. Lastly, coordination is examined via (i) toe tapping, and (ii) leg agility [24].

### Primary outcome

The primary outcome is gait adaptability as measured with the obstacle subtask of the Emory Functional Ambulation Profile (E-FAP). Participants are asked to negotiate a 10-m course in which two wooden blocks (100(l) × 10(w) × 5(h) cm) and a bin are placed along the walkway. The instruction given is to complete the task as fast as possible but keep your own safety in mind. The number of seconds needed to complete the task is registered. A faster time score indicates better gait adaptability. The obstacle subtask of the E-FAP has previously been used as an outcome measure for gait adaptability in several neurological populations [14, 15]. The full protocol is available online and via Wolf et al. [25].

### Secondary outcomes

Secondary outcome measures comprise of the following clinical tests:
10-Meter Walk Test (10MWT)

The *10MWT* is a standardized and recommended measurement of walking velocity. Participants walk 13 m in a straight line, first three times at comfortable speed and then three times as fast as possible. Participants have 3 m to accelerate to the requested speed. When the first foot crosses the 3-m line, the timer starts. The timer stops when the first foot crosses the 13-m line. Like this, the number of seconds it takes to walk 10 m is recorded [26]. The test has been found reliable, valid, and sensitive in neurological populations [26] and has been used in people with HSP [9, 13, 27, 28].
Mini Balance Evaluation Systems Test (miniBEST)

The *mini-BEST* is a 14-item, 3-point ordinal rating scale (0–2 points) to evaluate balance capacity in 4 subcategories: anticipatory postural control, reactive postural control, sensory orientation, and gait stability. The attainable sum scores range from 0 to 28 points, a higher score indicating better balance capacity. Participants perform the test barefoot. The full protocol is available online and has been described by Franchignoni et al. [29]. The mini-BEST is often used in neurological populations; has been found valid, reliable, and responsive [30–32]; and has been recommended for use in people with HSP [4].
Physical activity levels during daily life

*Physical activity* during daily life will be registered via the Activ8 Physical Activity Monitor (Activ8, Remedy Distribution Ltd., Valkenswaard, The Netherlands). The Activ8 monitor is a small (30 × 32 × 10mm) and lightweight device with three axial accelerometers. It registers body positions (non-wear of the Activ8/lying, sitting, and standing) and activities (walking, running, cycling) [33]. The Activ8 is placed by the primary researcher using Tegaderm™ tape on the right upper thigh of the participants. Interval for data sampling will be set to one measurement per 15 s. Collected measures consist of total time spent walking (minutes) and total time spent active (i.e., minutes classified as walking, running or cycling).
Activities-specific Balance Confidence scale (ABC)

*Balance confidence* will be measured using the ABC. The questionnaire describes sixteen indoor and outdoor situations. Participants are asked to express their confidence in safely executing the proposed situations without falling. Scores range from 0 to 100, a higher score indicating more confidence. The ABC has been used to assess balance confidence in people with HSP [27, 34]. The full questionnaire is available via Powell et al. [35].
Fall calendar

The *fall calendar* is used to monitor falls and near falls and is self-reported by the participants during a 15-week period. The World Health Organization defined a fall as “an event which results in a person coming to rest inadvertently on the ground or other lower level.” A near fall is defined as “a stumble event or loss of balance that would result in a fall if sufficient recovery mechanisms were not activated” [36]. In addition, participants register incidents where a fall was likely to happen, but was averted through the action of another person. When a (near) fall occurs, the participant is asked to report a short description of the event, the environment (indoor/outdoor, illuminated/dark space, and surface (e.g., tiles, carpet, forest)), and lastly, whether the (near) fall resulted in any injuries. To meet participants’ preference, calendars can be filled in digitally or on paper. Every other week, participants are reminded of the fall calendar via a phone call from the primary investigator (LV).
Walking Adaptability Ladder Test (WALT)

The *Walking Adaptability Ladder Test (WALT)* is a test to measure step precision. A standardized ladder is placed on the floor. It consists of 17 rectangular stepping targets that gradually decrease 2 cm in length (range 64–32 cm). Participants start stepping in the largest target and walk as fast as possible to the other side, turn and hit the targets in reverse order while avoiding the ladder rungs. The instructions are to perform the test as fast as possible, but try to prevent foot placement errors. The test is timed: a faster time is indicative of better stepping precision. Participants perform the test four times, first twice with one foot per target and, thereafter, twice with both feet in one target. A time penalty of 0.5 s is added each time a participant makes a foot placement mistake.
Spatio-temporal gait parameters

*Spatio-temporal gait parameters* are collected with a 3D full body gait analysis using Vicon (Vicon© Motion systems Ltd.) at the movement laboratory of the Radboudumc, Nijmegen. Retroreflective markers are placed on anatomical landmarks according to the standard Plug-in Gait marker model for upper and lower body. In addition, participants will wear accelerometers on their lateral heels, as the higher measuring frequency will enable a more accurate gait event detection. Participants will walk two bouts of 3 min over an 8-m walkway. The following spatio-temporal parameters will be retrieved: step length (cm), step width (cm), step time (s), walking speed (m/s), stride time (s), stride length (cm), and cadence (steps/min).

### Assessment of therapy adherence and co-interventions

To support adherence to the protocol, participants will be in direct contact with the primary investigator (LV) by telephone every other week. This enables the investigator to verbally confirm assessments and training dates, check adherence to the fall calendar, and quickly address and resolve questions and possible problems that may interfere with continuation of the protocol. In addition, participants are offered flexible time slots for the assessments and training sessions. Assessment of adherence to the C-Mill protocol is possible as therapists will log the performed C-Mill trainings. In case of an unexpected cancelation, the reason will be registered, and the missed training can be compensated in the next week. When multiple consecutive training sessions cannot proceed, a pragmatic solution is sought so that the participant is able to complete the protocol.

In addition, assessment of co-intervention will take place during the assessments. Participants are asked to self-report in a survey what type of co-intervention they received (e.g., physical therapy, occupation therapy).

### Sample size

Sample size calculation is based on previous studies assessing effectiveness of C-Mill training on the obstacle subtask of the E-FAP scores in neurological populations [14, 15]. A total of 32 participants is sufficient to demonstrate an improvement on the E-FAP score of 1.75 s (SD = 2.0 s, *α* = 0.05, *β* = 0.2). Considering a 10% attrition rate, 36 participants will be included.

### Statistical analysis

The effect of gait adaptability training on primary and secondary outcomes will be tested using ANCOVA. Post-intervention measurements will be used as dependent variables with pre-intervention measurements as the covariate. Group (C-Mill versus waiting list) is used as an independent between-subjects factors. The retention of gait adaptability training will be tested by merging both groups and using a repeated measures ANOVA with time as a within-subjects factor (C-Mill group: assessments 1, 2, and 3; waiting list: assessments 2, 3, and 4). Post hoc tests will be performed in the case of significant main or interaction effects, using paired *t* tests. Fall rates will be processed descriptively. Depending on the distribution of the data, the rate of near falls may be analyzed using Wilcoxon signed rank test. In addition, to determine key determinants of C-Mill training efficacy, a stepwise linear regression analysis will be performed with training-induced change in gait adaptability (relative change of the obstacle subtask of the E-FAP) as the dependent variable. Univariate analyses will be performed to select the best factors from the available demographic and clinical characteristics.

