### Group allocation and blinding

Participants will be allocated at random to the intervention group or to the (waiting list) control group following a 1:1 ratio. Randomization will be stratified based on disease duration (2 categories: 0–15 years; > 15 years) in blocks with a variable size (*n* = 4 or *n* = 6) to prevent an uneven distribution between groups. To determine disease duration, participants are asked for the year of symptom onset. Randomization will be performed in CastorEDC, a web-based data management system for academic studies (www.castoredc.com). Blinding of participants is not possible, as participants will know whether they receive C-Mill training or continue with usual care. The primary investigator (LV) takes part in the training sessions as a physical therapist and, therefore, cannot be blinded either.

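### The ANCOVA leaves out disease duration, the factor on which randomisation is stratified; if duration is prognostic beyond baseline, the test is conservative and attainable power is forgone

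*Protocol article*

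**What the plan says.** Under Group allocation and blinding, participants are allocated "following a 1:1 ratio", and "Randomization will be stratified based on disease duration" in two categories (0–15 years; more than 15 years), using blocks of 4 or 6. The stated purpose is "to prevent an uneven distribution between groups".

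Under Statistical analysis, "The effect of gait adaptability training on primary and secondary outcomes will be tested using ANCOVA". The model terms are then named: "Post-intervention measurements will be used as dependent variables with pre-intervention measurements as the covariate", and "Group (C-Mill versus waiting list) is used as an independent between-subjects factors". No stratum term appears there or elsewhere in the article. Disease duration otherwise appears only as a recorded demographic characteristic, which makes it available to the separate regression on determinants of training efficacy.

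Under Sample size, the planning target is an "improvement on the E-FAP score of 1.75 s" with an SD of 2.0 s, alpha 0.05 and beta 0.2. "A total of 32 participants is sufficient", raised to 36 for 10% attrition.

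**The concern.** Blocking within strata forces the two arms to be similar in disease duration. That removes between-stratum variation from the true sampling variance of the group difference. A model without the stratum still counts that variation as residual error. If the strata differ in outcome after baseline adjustment, the reported standard error exceeds the true one, the confidence interval is too wide and the p-value too large. The trial would then have balanced a factor by design without taking the precision that the balance makes available. With 32 evaluable participants planned, a few points of power are worth having when they cost almost nothing.

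**Working it through.** **Inputs from the article.** Difference 1.75 s; SD 2.0 s; alpha 0.05; power 0.80; 32 evaluable (16 per arm); 1:1 allocation in blocks of 4 or 6 within two strata; ANCOVA on group and pre score.

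**Assumptions not in the article.** Pre-post correlation 0.5; about half of participants in each stratum; two-sided test; a range of values for the share of post-score variance, left after baseline adjustment, that the stratum explains (partial R²).

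**Step 1: the plan's own figure.** By the normal approximation, n per arm = 2(z₁₋α/₂ + z₀.₈)² × SD²/Δ² = 2 × (1.960 + 0.842)² × 4/3.0625 = 20.5, so 21 per arm and 42 in total. This does not give 32. With the ANCOVA variance factor 1 − 0.5² = 0.75, 20.5 × 0.75 = 15.4, so 16 per arm and 32 in total, which matches. A one-sided test without that factor gives 17 per arm, 34 in total. The correlation of 0.5 is used below because it reproduces the stated 32 exactly; the article does not state it.

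**Step 2: what theory predicts.** The residual variance after baseline is 4 × 0.75 = 3. The stated model reports a standard error of about √(3 × 4/32) = 0.61 s, whatever the stratum explains. With perfect balance on the stratum, the true SD of the estimate is √(3(1 − R²) × 4/32). At R² = 0.20 that is √0.30 = 0.55 s, so the reported standard error would be about 12% too large. Incomplete final blocks reduce this somewhat in practice.

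**Step 3: simulation.** 12,000 trials per scenario; permuted blocks of 4 or 6 within two strata; N = 32; total residual variance held at 3 throughout; two-sided 5% test. The standard error, true SD and type I error come from runs with no treatment effect, and power from runs with a 1.75 s effect.

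| Partial R² | Reported SE, stated model | True SD, stated model | Type I error, stated | Type I error, with stratum | Power, stated | Power, with stratum | Power forgone (points) |
|---|---|---|---|---|---|---|---|
| 0 | 0.617 | 0.625 | 5.3% | 5.2% | 77.3% | 77.1% | about 0 |
| 0.02 | 0.619 | 0.617 | 4.6% | 4.8% | 77.6% | 78.0% | 0.4 |
| 0.05 | 0.619 | 0.617 | 4.6% | 5.2% | 78.0% | 79.6% | 1.6 |
| 0.10 | 0.619 | 0.598 | 4.1% | 5.1% | 78.8% | 81.8% | 3.0 |
| 0.20 | 0.621 | 0.569 | 3.2% | 5.2% | 79.1% | 85.7% | 6.6 |
| 0.30 | 0.622 | 0.533 | 2.2% | 5.2% | 80.7% | 90.1% | 9.4 |

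Simulation error is roughly 0.2 points for type I error and 0.4 points for each power figure. The 5.3% at R² = 0 is therefore not evidence of inflation. The reported standard error is too large by about 4% at R² = 0.10 (0.619/0.598), 9% at 0.20 (0.621/0.569) and 17% at 0.30 (0.622/0.533).

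**Step 4: what these R² values mean in seconds.** With equal strata, the stratum difference given baseline is 2 × √3 × √R². That is 0.77 s at R² = 0.05, 1.10 s at 0.10 and 1.55 s at 0.20. The last is close to the treatment effect the trial is sized to find.

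**The case against.** The strongest objection is that the loss is conditional and may be negligible. The covariate is the same person's time on the same test about six weeks earlier (weeks 16 and 22), which probably absorbs much of what disease duration says about the post score. The article gives no figure for what remains. At a partial R² of 0.05 or less the loss is under 2 points. This stands: a reader might infer that the standard errors are certainly too large, and the article does not support that.

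A reader might also infer that power falls far below plan. Adding a stratum difference of 1.0 or 1.5 SD on top of a fixed residual variance does give about 66% or 53% for the stated model. But with a residual variance of 0.75 (in units of SD²), those differences are partial R² values of 0.25/(0.25 + 0.75) = 0.25 and 0.5625/(0.5625 + 0.75) = 0.43, in trials noisier than the planning SD of 2.0 s. With total variance held fixed, the stated model's power does not fall: it runs from 77.3% to 80.7% across the table. What is at issue is a gain not taken.

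Nor does this point show that the trial misses its planned power. That is a separate matter, which turns on whether 2.0 s is a raw, change or residual SD and on whether the test is one- or two-sided; the article states neither.

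Finally, the article condenses a full protocol (version 5) that is not shown, and a stratum term might be specified there or in an analysis plan. This carries less weight, because the article does not leave the model open: it names the outcome, the covariate and the factor.

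**Conclusion.** The mismatch between design and stated model is real; its consequence is conditional. If disease duration is prognostic beyond baseline, the stated ANCOVA is conservative and forgoes attainable power. Under the assumptions above, this is immaterial up to a partial R² of about 0.05 and worth recovering from about 0.10. The article offers some reason to think duration could matter: it describes the disease as progressive, makes duration its only stratification factor and sets no limit on symptom duration. None of this fixes the size.

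The validity of the result is not threatened. Any error is towards caution. The point is a small efficiency improvement, worth making because the choice is lopsided: including the term costs almost nothing if the stratum is irrelevant, and leaving it out may cost several points if it is not.

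**What to change.** In Statistical analysis, add the disease-duration stratum (0–15 versus more than 15 years) as a fixed factor in the ANCOVA for the primary outcome and for the secondary outcomes analysed by ANCOVA. Use the category recorded at randomisation. Disease duration is also collected at the week-16 assessment, after allocation, and a participant near the 15-year boundary could be classified differently there.

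Prespecify the term before outcome data are analysed. Because the assessor is unblinded, a covariate added later would be open to challenge. The article reports that no laboratory assessments had been conducted when it was written, so it could have been added cleanly at that stage. If the full protocol or an analysis plan already contains the term, only the published description needs correcting.

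The cost is one phrase and one degree of freedom: 77.1% power instead of 77.3% if the stratum is not prognostic, a difference within simulation error.

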### Objectives

This study aims to provide an essential step towards evidence-based and individually tailored gait rehabilitation in people with HSP. The objectives are twofold:
To study the effect of ten 1-h sessions of C-Mill training on gait adaptability in people with pure HSP.To identify key determinants of C-Mill training efficacy in people with pure HSP.

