## Discussion

Limitations in walking capacity are among the most disabling symptoms in people with hereditary spastic paraplegia (HSP). A handful of studies aimed to improve walking capacity in people with HSP [9, 13, 37], but these studies did not include context-specific exercises aimed at gait adaptability. Gait adaptability has been successfully trained in several neurological populations using augmented reality on the C-Mill [14, 15], but so far, this has never been done in people with HSP.

Move-HSP is a two-armed, open-label randomized controlled trial that will be the first study to assess the effects of gait adaptability training in people with pure HSP. Participants in the intervention group receive 10 h (1-h sessions; twice per week) of protocolled C-Mill training, whereas the control group continues with treatment as usual (waiting list). After 5 weeks on the waiting list, the control group will cross over and follow gait-adaptability training. The primary outcome is gait adaptability assessed with the obstacle subtask of the E-FAP. Secondary outcomes focus on several aspects of balance and gait capacity. Mildly to moderately affected people with pure HSP that fit the a-priori established eligibility criteria will be included. There are no restrictions regarding sex, symptom duration, or use of orthotic/orthopedic devices in order to represent the clinical heterogeneity characteristic of people with pure HSP. Yet, to provide proof op principle and limit the influence of impaired cognitive capacity, people with complex forms of HSP are excluded.

Move-HSP aims to make a step towards evidence-based and individually tailored gait rehabilitation programs for people with HSP. It will reveal whether context-specific training is an effective tool for improving gait adaptability in people with pure HSP. If the C-Mill intervention results in improved walking adaptability, it may be beneficial to implement this type of training on a regular basis in the rehabilitation of people with HSP. In addition, knowledge of the key determinants of training efficacy will help to optimize the selection of subjects with HSP that are most responsive to gait adaptability training.

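### Objective 2 picks key determinants by univariate screening and then stepwise regression on at most 36 people, so false determinants are named far more often than 5% and R-squared is overstated

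*Protocol article*

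**What the plan says.** The Objectives section gives two aims of equal standing. The second is "To identify key determinants of C-Mill training efficacy in people with pure HSP".

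The Statistical analysis section fixes the method: "a stepwise linear regression analysis will be performed with training-induced change in gait adaptability", with the outcome defined as "relative change of the obstacle subtask of the E-FAP) as the dependent variable". It adds that "Univariate analyses will be performed to select the best factors from the available demographic and clinical characteristics". I read this as a univariate screen that feeds a stepwise model, both on the same participants.

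The pool is described only as what is available. The Demographic and clinical assessments section lists what is collected, much of it by muscle and side, for example: "Bilateral muscle strength is scored with the Medical Research Council (MRC) scale".

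The number of people comes from the Sample size section, which deals with the primary comparison: "A total of 32 participants is sufficient to demonstrate an improvement on the E-FAP score of 1.75 s" and "Considering a 10% attrition rate, 36 participants will be included".

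On use, the Discussion says that "knowledge of the key determinants of training efficacy will help to optimize the selection of subjects with HSP".

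**The concern.** The data choose the predictors twice, first in the screen and then in the stepwise fit, and the same data then supply the p-values, coefficients and R-squared of the chosen model. Those quantities are computed as if the model had been fixed in advance. After selection, the p-values no longer have their nominal error rate, the coefficients of selected predictors are too large on average, and R-squared is too high.

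The problem grows with the number of candidates. Here there may be about as many candidates as people, or more. A small sample adds instability, in that a few different participants could change which factors are named.

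At stake is one of the two objectives, and a result that the authors expect to help choose suitable patients. The randomised comparison on the E-FAP obstacle subtask is a separate ANCOVA and is not touched.

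**Working it through.** **1. People.** The plan's enrolment figure follows from its evaluable figure: 32 / (1 - 0.10) = 35.6, rounded up to 36. No size or error rate is given for the determinant analysis. I take n = 32 and n = 36, which assumes that everyone who trains enters the regression. The article says the groups are merged for the retention analysis but does not say so for this one. With the intervention arm alone, n would be about 16-18.

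**2. Candidates**, counted from the Demographic and clinical assessments section:

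- Demographic, 12: age, sex, height, weight, genetic diagnosis, inheritance, disease duration, medication, orthopedic shoes or orthoses, other walking aids, visual deficits, falls.
- Clinical, one score per domain, 7: SPRS, MRC, MAS, vibration, TCMS, toe tapping, leg agility. Total 12 + 7 = 19.
- Clinical, itemised: SPRS 1, MRC 8 x 2 = 16, MAS 5 x 2 = 10, vibration 3 x 2 = 6, TCMS 1, coordination 2. Total 12 + 1 + 16 + 10 + 6 + 1 + 2 = 48. Splitting the ankle MAS by knee position adds 4, giving 52.

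People per candidate: 32/19 = 1.7 to 36/19 = 1.9, or 32/48 = 0.67 to 36/48 = 0.75.

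**3. Closed form.** Assumed thresholds are a screen at p<0.10 and entry at p<0.05. The first stepwise entry is the candidate with the smallest univariate p-value, so at least one candidate is named whenever that p-value is below 0.05. With k independent candidates and no true predictor, the probability is 1 - 0.95^k:

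- k = 10: 40%
- k = 13: 49%
- k = 14: 51%
- k = 19: 62%
- k = 48: 91.5%

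Sample size does not enter this formula. The candidate count and the entry threshold drive the rate.

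**4. Simulation of the two-step rule** (screen 0.10, entry 0.05, removal 0.10, outcome unrelated to every predictor; 1,000 runs per scenario, or 3,000 for the third row; Monte Carlo standard error about 1.5 points at 1,000 runs):

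| Candidates | Correlation | False naming, n=32 / n=36 | Mean R-squared when any selected, n=32 / n=36 |
|---|---|---|---|
| 10 | none | 41% / 40% | 0.206 / 0.186 |
| 19 | none | 60% / 64% | 0.237 / 0.212 |
| 19 | 7 clinical scores at 0.5 | 59% / 59% | 0.229 / 0.206 |
| 48 | none | 91% / 90% | 0.355 / 0.315 |
| 48 | MRC, MAS and vibration items at 0.5-0.8 within domain | 75-85% / 77-84% | 0.276-0.306 / 0.242-0.271 |
| 19 | all at 0.3 | 50% / 49% | 0.205 / 0.188 |
| 19 | all at 0.7 | 29% / 29% | 0.185 / 0.166 |
| 48 | all at 0.7 | 40% / 41% | 0.194 / 0.167 |

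A repeat simulation gave 62-64% for 19 independent candidates, 57-59% with within-domain correlation, and 91-92% for 48 independent candidates. Combined ranges are therefore 57-64% for 19 and 75-92% for 48, leaving aside correlation across all candidates.

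**5. Why R-squared is inflated.** To enter first at p<0.05, a predictor needs r-squared of at least t²/(t² + n - 2). For n = 32 this is 2.042²/(2.042² + 30) = 0.12; for n = 36 it is 2.032²/(2.032² + 34) = 0.11. Any selected model therefore shows more than this even when the true value is 0.

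**6. A short fixed list.** At 0.05 each, 3 candidates give 1 - 0.95³ = 14% and 4 give 1 - 0.95⁴ = 19%. Bonferroni thresholds would be 0.05/3 = 0.017 and 0.05/4 = 0.0125.

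**The case against.** The strongest reply is that the numbers rest on inputs the article does not give. It lists no candidates for the regression, and reaching 48 requires each muscle, side and site to be a separate predictor, which no section says. The thresholds are mine. Independence is unrealistic for left and right scores in the same legs. A condensed article may leave the list, scoring and thresholds to a fuller document. All of this stands, and it is why the size is a range. It does not rescue the method, because data-driven selection in two steps on the same people is what the article states. With only 10 independent candidates the rate is still about 40%.

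A reader might infer three stronger points that the document does not support:

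- *The procedure yields determinants whether or not any exist.* It does not always do so: with 19 candidates, 36-43% of null trials name none, and with 10 independent candidates about 60% name none. More often than not also needs about 14 or more independent candidates.
- *The result will decide who receives training.* The Discussion says only that it will help optimise selection, within a step towards tailored rehabilitation. No allocation rule is planned.
- *No shrinkage or validation is planned.* The article is silent, and silence in a condensed article does not show this.

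It is also fair to say that the trial is framed as proof of concept. That wording concerns the efficacy of training; the determinant analysis is not called exploratory anywhere in the article.

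**Conclusion.** The point holds as a criticism of the stated method. Screening followed by stepwise regression on at most 36 people gives p-values, coefficients and R-squared that are not valid as they would ordinarily be reported.

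The false-naming rates of about 40%, 57-64% and 75-92% for 10, 19 and 48 candidates are illustrative. They assume no true predictor, the thresholds above, and at most within-domain correlation. Uniform correlation of 0.7 across all candidates, which is implausible for a list containing age, sex and height, still gives 29% with 19 and about 40% with 48, far above 5%. Looser entry thresholds would raise every figure. Confidence is high in the criticism of the method and lower in any single percentage.

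The matter should be corrected, but it does not affect the primary analysis.

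**What to change.** Before outcome data are seen, replace the screen and the stepwise step with one linear model. It should contain at most three or four candidates chosen in advance by the investigators, all entered together with the pre-training E-FAP obstacle time and all reported whatever their p-values. State how multiplicity is handled: unadjusted at 0.05 each, the chance of at least one false determinant is about 14-19%; either acknowledge this or adjust for it.

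If a wider search is wanted, use penalised regression with bootstrap optimism correction of R-squared and report how often each candidate is selected. Say plainly that selection is unstable at this sample size.

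In both the Statistical analysis section and the Discussion, describe the result as hypothesis-generating.

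The cost is a change of wording and some analysis work, with no extra participants, visits or measurements. The drawback is that fewer predictors can be examined or claimed. The Trial status section reports that no laboratory assessments had yet taken place, so at that point the model could be fixed without knowledge of the outcome.
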